## Abstract

**Background:**

Major depressive disorder (MDD) is highly prevalent and associated with substantial disease burden and significantly reduced life expectancy. Physical activity (PA) has been shown to reduce depressive symptoms to a similar extent as antidepressant medication. Despite this evidence, individuals with MDD engage in lower levels of PA and exhibit higher levels of sedentary behavior. Structural, physical, and psychological barriers hinder PA engagement. PA coaching offers a promising strategy to overcome these barriers and promote sustainable behavior change. Previous research highlights the importance of addressing affective responses to PA in interventions. Moreover, the support of technology-based tools, such as wearables, seems promising. This study aims to investigate the short- and long-term effects of a new PA coaching approach on PA behavior, depression severity, and quality of life in outpatients with MDD. Potential mechanisms of behavior change and participant experiences are also examined.

**Methods:**

This study uses a three-arm randomized controlled trial (RCT) design and is conducted at a psychiatric day clinic in German-speaking Switzerland. A total of 114 individuals aged 18 to 65 years with a clinical diagnosis of MDD (ICD-10: F32 and F33) are recruited on an ongoing basis and randomly assigned to one of three groups: (1) A 10-week PA coaching program based on interest and experience in PA, supported by a wearable smart ring for self-monitoring; (2) the same 10-week program extended by an additional, remote 26-week cognition-based coaching phase; or (3) a control group receiving treatment as usual along with written current PA guidelines. Data is collected at three measurement timepoints: 2-4 weeks after the start of day clinic treatment (baseline), after the 10-week coaching phase (post), and after a 6-month follow-up period (follow-up). The primary outcome is the change in device-measured PA over time (baseline, post, and follow-up), measured via Fibion^®^ accelerometer, and analyzed using linear mixed models.

**Discussion:**

A new PA coaching program is introduced to counteract low PA levels observed in individuals with MDD. By combining affective with cognitive components of behavior change, the intervention aims to promote a sustainable increase in PA and ultimately improve mental and physical health and quality of life.

**Trial registration:**

DRKS: DRKS00036209. Registered on 08 May 2025

**Supplementary Information:**

The online version contains supplementary material available at 10.1186/s13063-026-09500-1.

## Introduction

### Background and rationale {6a}

Major depressive disorder (MDD) is among the most prevalent mental health conditions worldwide, affecting an estimated 332 million people in 2021, corresponding to a global prevalence of 4% [1] and a lifetime prevalence of 11% [2]. In 2022, disability-adjusted life years (DALYs) attributable to MDD reached 50 million, with projections indicating an increase to 68 million by 2050 [3]. A key factor in the disabling nature of MDD is its negative impact on health-related quality of life [4]. Beyond impairing daily functioning and overall well-being, MDD generates considerable economic costs. Indirect costs — such as household expenses, presenteeism, and absenteeism — are about as high as direct healthcare costs [5]. Individuals with severe mental illness, including MDD, face a 2- to 3.5-fold increase in all-cause mortality risk compared to the general population [6]. Accordingly, individuals with severe mental illnesses experience a 20% reduction in life expectancy and are estimated to die, on average, 10 to 25 years earlier than the general population [7–11]. While elevated mortality from unnatural causes such as suicide, accidents, and substance misuse contributes significantly to this disparity [7, 12, 13], the majority of excess deaths are due to natural causes, particularly cardiovascular disease, respiratory conditions, and infectious diseases [14–20].

Given the high prevalence and substantial burden of MDD, identifying effective treatment strategies is of critical importance [21]. Current clinical treatment guidelines recommend psychotherapy and/or pharmacological antidepressants as first-line treatments for MDD [22, 23]. However, antidepressant use is frequently accompanied by side effects — such as nausea, weight gain, incontinence, and sexual dysfunction [24, 25] — as well as low adherence rates [26] and limited efficacy [27, 28]. Approximately, 30% of patients do not respond to first-line treatment, and even after medication switches or augmentation, persistent non-response and adverse effects remain a major clinical challenge [29–31].

In light of these limitations of standard care, exercise has gained increasing attention as a non-pharmacological approach to alleviating depressive symptoms. Compelling evidence suggests that physical activity (PA) interventions produce moderate to large antidepressant effects [32, 33]. The effect of exercise has even been demonstrated to be comparable to antidepressant medication [34], as confirmed by several meta-analyses [35–37]. Furthermore, regular exercise following the treatment period has been found to decrease the rate of relapse by 50% after 6 months [38]. Beyond its antidepressant effects, PA has also been associated with improvements in broader health outcomes, including health-related quality of life [39], cardiovascular risk [21, 40], cognition [41], sleep [42], and potential biomarkers of depression such as cortisol levels [43]. Owing to the well-documented benefits of exercise in the treatment of depression, PA is now recommended as an effective complementary treatment modality in several national and international clinical guidelines [44–48].

Despite strong evidence supporting exercise as a treatment for depression, its inclusion in clinical guidelines, and its adoption by an increasing number of clinics as a standard therapy [49, 50], PA levels among adults with depression remain significantly lower than in the general population. Data indicate that approximately 86% of individuals with depression do not meet recommended PA levels and tend to engage in more sedentary behavior compared to people without depression [51]. Explanations for the discrepancy between the well-established efficacy of PA and actual PA behavior can, on the one hand, be identified within clinical practice: although PA programs are available in almost all psychiatric hospitals in Switzerland, only about one in four patients utilize them [49]. This underutilization reflects a broader trend of PA being insufficiently prescribed to individuals with MDD [49]. Key contributing factors include limited training among treatment personnel, skepticism regarding patient adherence, and a lack of collaboration with exercise specialists [52].

On the other hand, at the individual level, people with depression face both physical and psychological barriers to engaging in regular PA. Common barriers include (higher levels of) depression symptoms, higher body mass index (BMI), and the presence of somatic comorbidities [53]. In addition, motivational and volitional deficits in all areas of daily life interfere with the aim of engaging depressed patients in more exercise and PA. Individuals with MDD demonstrate fewer action plans, have less maintenance self-efficacy, and are more easily distracted by barriers [54, 55]. These challenges highlight the need for targeted interventions that provide patients with professional support to enable them to overcome barriers and adopt a physically active lifestyle [53, 56, 57]. In addition, it is important to put effort into the promotion of behavioral skills necessary for patients to build up and maintain PA [46, 56].

Given this background, PA coaching has proven to be feasible and well accepted in inpatients with MDD, as demonstrated in a recent RCT [58, 59]. Despite the feasibility and acceptance, no long-term effects on PA behavior were observed [60]. A qualitative evaluation of the intervention identified several participant-reported challenges, including limited contact during predominantly remote coaching sessions held at 2-week intervals and the absence of structured support following the intervention period [61]. These findings highlight the need for strategies that foster sustained PA behavior beyond the duration of the coaching itself.

PA coaching in PACINPAT was based on the motivation-volition (MoVo) process model [62] and behavior change techniques [63], both grounded in social-cognitive approaches to behavior change. Recent advances in exercise psychology emphasize the role of affective as well as cognitive determinants of behavior [64–68]. The Affective-Reflective Theory of physical inactivity and exercise (ART) distinguishes two coexisting processes: an automatic affective valuation and a reflective cognitive process [64]. In MDD, diminished motivation and volition may reduce the impact of the cognitive reflective process on activity decisions [54, 64], making the enhancement of positive affective responses to PA a promising strategy for both initiating and maintaining long-term participation in PA [69–72].

In addition, emerging technologies, such as wearables, offer substantial potential for supporting exercise behavior change [73–75]. Integrating such technologies into future coaching interventions may enhance monitoring of PA behavior for both patients and coaches. Moreover, wearables can support the sustainability of intervention effects by enabling self-monitoring to continue after the formal coaching has ended [76].

## Objectives {7}

Building on the background outlined above, the primary objective of this study is to examine the short- and long-term effects of a novel PA coaching program to promote PA behavior in outpatients with MDD receiving treatment as usual. The intervention consists of a structured PA coaching approach that integrates both affective (interest- and experience-based) and cognitive (reflective) strategies to facilitate the adoption of a sustainable PA routine. To enhance engagement and adherence, participants are also supported through continuous self-monitoring using a commercially available smart ring.

Secondary objectives are (i) to assess short- and long-term effects of the PA coaching program on quality of life and depression severity and (ii) to investigate potential mechanisms responsible for the targeted behavior change.

## Trial design {8}

This study is a single-center, three-arm randomized controlled trial (RCT) with an allocation ratio of 1:1:1. It includes two intervention groups (IG1, IG2) and one control group (CG) and follows an open-label design. The trial is conducted in collaboration between the Sonnenhalde AG Psychiatric Clinic, Riehen, Switzerland, and the Department of Sport, Exercise and Health (DSBG) at the University of Basel, Basel, Switzerland.

The intervention is delivered in an outpatient setting, recruiting patients from day clinics of the Sonnenhalde AG. Assessments are conducted at three time points: (a) baseline (T0), (b) post-intervention (T1, 10 weeks after baseline), and (c) follow-up (T2, 36 weeks after baseline). The follow-up period of 26 weeks after post-intervention ensures alignment with prior comparable studies [77–79]. All assessments are conducted on-site at the day clinics.

An overview of the study design is provided in Fig. 1. The protocol is designed in accordance with the SPIRIT 2025 statement for interventional trials [80].

**Fig. 1 Fig1:**
[figure not shown]
Overview of the study design

Participants (*N* = 114) are randomized (stratified by sex and age) to one of two PA coaching conditions (with or without continuous support after post-intervention) or to a control condition (written information on health-enhancing PA) [81]. Given the behavioral nature of the intervention, neither participants nor researchers are blinded. To reduce assessment bias, the primary outcome (PA behavior) is assessed device-based using a thigh-worn accelerometer device.

The trial features several pragmatic elements [82–84], such as integration into treatment as usual, delivery in real-world and authentic settings (e.g., home-based components), and use of a commercially available smart ring for self-monitoring. Coaching protocols are adapted for clinical populations, and outcomes focus on clinically relevant indicators, including depressive symptom severity and quality of life.

## Methods: participants, interventions, and outcomes

### Study setting {9}

The study is conducted from summer 2025 until autumn 2027 at day clinics of the Sonnenhalde AG Psychiatric Clinic by the Department of Sport, Exercise and Health (DSBG) of the University of Basel.

### Eligibility criteria {10}

Participants are eligible for participation in the study if they are 18 to 65 years old, are receiving outpatient treatment at the day clinic, and are diagnosed with a depressive disorder (F32, F33) by a physician. Further inclusion criteria are sufficient German language skills, signed informed consent, and voluntary participation.

Exclusion criteria are medical contraindications to PA, as assessed by a physician or indicated by the Physical Activity Readiness Questionnaire (PAR-Q) [85], current psychosis and/or acute suicidality, and pregnancy or breastfeeding at the time of assessment. In cases where medical contraindications are initially present, participants may still be enrolled if they provide written confirmation from their general practitioner (or from another physician) stating that participation in PA is medically acceptable.

### Who will take informed consent? {26a}

At the beginning of their day clinic treatment, patients receive an information folder including a flyer about the PACOUTPAT study. Study personnel from the University of Basel are present 2 days per week, and interested patients are invited to a one-on-one meeting with a study team member, where detailed oral and written information is provided. The researcher explains the study’s purpose, procedures, duration, potential risks and benefits, and the voluntary nature of participation. It is emphasized that withdrawal from the study is possible at any time without negative consequences. Patients receive a participant information sheet and an informed consent form. They are given up to 1 week to ask questions or request further details before deciding. Written informed consent is obtained prior to any study procedures.

### Additional consent provisions for collection and use of participant data and biological specimens {26b}

Not applicable as no further use of participant data is planned and no biological specimens are collected.

## Interventions

### Explanation for the choice of comparators {6b}

By comparing PA coaching interventions (IG1 and IG2) with standard treatment (CG), this study assesses the effectiveness and potential superiority of PA coaching in increasing PA, alleviating depressive symptoms, and enhancing quality of life. Furthermore, the comparison between a 10-week coaching intervention (IG1) and an extended version that includes an additional 6 months of support (IG2) provides insights into the impact of coaching duration on the sustainability of PA engagement, depression severity, and health-related quality of life. The inclusion of standard treatment across all groups ensures a pragmatic, real-world approach, allowing for a meaningful evaluation of the added benefits of PA coaching within routine clinical care.

### Intervention description {11a}

Participants in both intervention groups continue to receive treatment as usual according to the Swiss treatment guidelines for MDD [86]. The intervention is designed to provide individually tailored support and encouragement to increase PA during and after clinical outpatient treatment for a period of up to 36 weeks (= 10 + 26 weeks).

### Intervention Group 1

Participants in IG1 receive a 10-week PA coaching program guided by a trained personal PA coach. The coaching follows an interest- and experience-based approach aimed at identifying PA opportunities that align with participants’ individual preferences and promote positive affective experiences. Where appropriate, structured PA is preferred over unstructured forms to leverage the benefits of group-based and/or supervised exercise, such as increased social support and accountability. The coaching approach is individualized and flexible, supporting unstructured PA when it better matches the participant’s interests and enjoyment. The primary focus is on promoting pleasure and well-being during PA with the ultimate goal of facilitating long-term adherence.

The coaching begins with a 60-min introductory session during which the coach and participant get to know each other, review the structure and goals of the program, and assess the participants’ current life situation and PA status using a standardized questionnaire [87]. Participants’ previous PA experiences and preferences are also explored. To identify individual motives and goals related to PA, the Bernese Motive and Goal Inventory [88] is administered.

In the second session, these motives and goals are reviewed and reflected upon to derive personal implications for PA engagement. A first structured PA session is identified, and relevant logistical and motivational conditions for attendance are established. The third session involves attending this first exercise session together with the coach providing on-site support. During this and subsequent sessions, affective responses are monitored using the Feeling Scale [89], the Felt Arousal Scale [90] is used to assess perceived activation, and the Borg Perceived Exertion Scale [91] is administered for the definition of exertion.

Sessions 4 to 9 alternate between attending structured PA sessions and reflective sessions. These reflective coaching sessions involve evaluation of experiences, discussing whether specific activities should be continued or adapted, and planning future participation to optimize enjoyment and fit with individual preferences.

All 10 coaching sessions are conducted face-to-face in the participant’s personal environment to maximize individual support and real-world applicability. Each session is scheduled to last approximately 60 min.

To further facilitate behavior change, the coaching is supported by a wearable smart ring, adhering to 12-point WATCH (Wearable Activity Tracker Checklist for Healthcare) guidelines [92]. Specifically, the Oura Ring (Generation 3; Ōura Health Oy, Finland) is used. The lightweight device (4–6 g) includes a 50-Hz triaxial accelerometer, NTC thermistor, and photoplethysmograph to continuously measure movement, body temperature, heart rate, heart rate variability, and respiration [93]. The ring is worn on the nondominant hand (index, middle, or ring finger). The device comes with a 6–7-day battery life and uploads data to both a smartphone app and a secure cloud dashboard. This allows coaches to monitor participants’ PA levels, energy expenditure, and sleep patterns. Participants in IG1 continue to wear the ring after the end of the 10-week coaching program until follow-up.

### Intervention Group 2

Participants assigned to IG2 receive the same 10-week interest- and experience-based coaching as IG1 and also continue to wear the Oura Ring until follow-up. However, unlike IG1, IG2 remains in contact with the coach for an additional 6 months (26 weeks) to receive cognition-based coaching aimed at promoting sustainable behavior change.

During this phase, biweekly phone calls are conducted to assess participants’ PA habits and adherence to their routines, offering support if difficulties arise. These brief (~20-min) phone sessions focus on applying evidence-based behavior change techniques (BCTs) to reinforce long-term habit formation [94]. Strategies include structured activity planning, identifying and overcoming barriers, leveraging social support, and relapse management. The goal is to enhance self-regulation and resilience, ensuring that participants maintain their achieved activity levels beyond the initial intervention period. A detailed description of the intervention procedures is provided in the Intervention Guide, which is available as Additional file 1.

### Dose rationale for intervention groups

Exercise guidance in this trial is informed by the World Health Organization’s recommendations, which advise a minimum of 150 min of moderate-intensity or 75 min of vigorous-intensity aerobic PA per week or an equivalent combination of both [95]. However, these targets may not be attainable for all individuals with MDD, and, conversely, some participants may already meet them at baseline [60]. Therefore, the intervention emphasizes an individualized, adaptable approach. Recent evidence indicates that as little as 50 min of moderate-intensity aerobic exercise per week can reduce depressive symptoms, with optimal effects observed at approximately 140 min weekly [96]. Participants are encouraged to increase their activity at any level, highlighting the benefits of even light-intensity movement [97, 98]. PA recommendations are framed as aspirational and adaptable, aligning with current efforts to reframe PA guidelines in a more effective manner [99, 100]. A gradual, stepwise progression toward an active lifestyle is promoted, emphasizing enjoyment, feasibility, and sustainability. To support individual preferences and enhance engagement, a range of activity types is encouraged, including aerobic and resistance training, yoga, and individual and team sports.

### Control group

The control group (CG) receives treatment as usual provided by the day clinic, along with standardized written information on the health benefits of PA. Specifically, they are sent a 62-page booklet titled *Bewegungsempfehlungen Schweiz: Grundlagen*, published in 2022 by the Swiss Federal Office of Sports in collaboration with other members of the “hepa” network [81].

### Criteria for discontinuing or modifying allocated interventions {11b}

Participants can withdraw from the study at any time without providing a reason and without any impact on their medical care. Participants are asked to discontinue from the study if they develop any cardiovascular, metabolic, neurological, pulmonary, or orthopedic complications that could limit the safety of participation in PA. Further, female participants who become pregnant during the course of the project are excluded due to the considerable influence of pregnancy on PA behavior [101, 102].

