### Plans to promote participant retention and complete follow-up {18b}

In week 26 of the 36-week study period, corresponding to 16 weeks post-completion of the day clinic treatment, participants in all three groups receive a small token of appreciation by mail from the study team. The token consists of a thank-you postcard, a small motivational sticker, and a piece of chocolate. All items are non-monetary and of minimal value and are intended to acknowledge participants’ contributions to the study and to promote sustained engagement in the completion of follow-up study procedures.

For participants allocated to the intervention groups, upcoming data assessments are integrated into ongoing coaching sessions as part of the established protocol. In contrast, participants in the control group are notified of forthcoming assessments via written communication.

Importantly, individuals who discontinue participation in the intervention are still invited to complete scheduled data assessments, thereby supporting the integrity and completeness of longitudinal data collection.

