### Methods in analysis to handle protocol non-adherence and any statistical methods to handle missing data {20c}

All study variables will be screened for missing data, outliers, and multicollinearity. Missing data patterns will be examined descriptively and visually, with Little’s MCAR test as a supplementary tool. The most plausible missing data mechanism (MCAR, MAR, or MNAR) will be inferred from these observations, study design, and theoretical considerations, and sensitivity analyses will be conducted to assess robustness [165]. If data are plausibly MCAR or MAR, appropriate imputation methods (e.g., multiple imputation) will be applied [166].

The primary analysis will follow the intention-to-treat (ITT) principle, including all participants as randomized and using the chosen imputation methods for missing data [166]. This approach estimates the effectiveness of the interventions under real-world conditions [167, 168]. A secondary per-protocol (PP) analysis, including only participants who adhered to the study protocol, will be conducted to estimate the intervention effect under ideal adherence [167].

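### Item 11b takes participants with complications or pregnancy out of the study rather than only out of the coaching, so their later PA is lost for outcome-related reasons; the effect is probably small and cheap to avoid

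*Protocol article*

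**What the plan says.** Item {11b} of the protocol article is headed as criteria for discontinuing or modifying the allocated interventions. Apart from voluntary withdrawal, it names two events:

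- Complications: "Participants are asked to discontinue from the study if they develop any cardiovascular, metabolic, neurological, pulmonary, or orthopedic complications that could limit the safety" of taking part in PA.
- Pregnancy: "female participants who become pregnant during the course of the project are excluded due to the considerable influence of pregnancy on PA behavior".

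The retention section {18b} says that "individuals who discontinue participation in the intervention are still invited to complete scheduled data assessments".

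On analysis, {20c} says: "The primary analysis will follow the intention-to-treat (ITT) principle, including all participants as randomized", with imputation for missing values, and gives the purpose: "This approach estimates the effectiveness of the interventions under real-world conditions". On missing data it says: "The most plausible missing data mechanism (MCAR, MAR, or MNAR) will be inferred from these observations, study design, and theoretical considerations", and adds that "sensitivity analyses will be conducted to assess robustness".

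The primary outcome is device-measured PA from a thigh-worn sensor over 7 days at T0, T1 (week 10) and T2 (week 36). The model in {20a} uses T1 and T2 as outcomes and T0 as a predictor. Randomisation follows the baseline assessment ({16c}).

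**The concern.** The heading of {11b} is about the intervention, but the consequence it states falls on study participation. Both events bear on the primary outcome. The complications count because they limit safe PA, and pregnancy leads to exclusion expressly because it changes PA. A randomised person is therefore dropped for a reason tied to the value that would have been measured.

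Injury and pregnancy are part of the real-world conditions under which {20c} wants to estimate effectiveness. The missing values are probably low ones. An analysis that fills them in from unaffected members of the same arm would raise that arm's mean. If such exits are more common under coaching, the coaching effect is overstated. T2 is the more exposed time point: it carries the long-term effect in the primary objective and is lost for every exit under the rule.

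Much of the loss is avoidable. The sensor records daily life and requires no exercise, and {18b} already provides for assessing people who are off the intervention.

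**Working it through.** **Reading the sections together.** {11b} sends people out of the study. {18b} keeps inviting those who stop the intervention. No section keeps assessments going for those removed under {11b}. T0 is complete before allocation. An exit before week 10 loses T1 and T2, and a later exit loses T2 only.

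**The plan's own figures.** With f = 0.175, r = 0.50, alpha = 0.05, three groups and three time points, the group-by-time test of a repeated-measures ANOVA needs N = 87 (power 0.903), as {14} states. 87 × 1.3 = 113.1, which rounds up to 114 in three equal arms of 38. The margin above 87 is 114 − 87 = 27.

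**Assumptions, none from the documents.**
- Event rates over 36 weeks, coached/control: 5%/2% (low) or 10%/3% (high).
- PA after the event lower by d = 0.5 (low) or 1.0 SD (high).
- Events spread evenly over the 36 weeks.

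**Number leaving** (76 coached, 38 control).
- Low: 0.05 × 76 + 0.02 × 38 = 4.6.
- High: 0.10 × 76 + 0.03 × 38 = 8.7.
- Also without T1 (× 10/36): 1.3 and 2.4.
- Share of the margin of 27: 17% and 32%.

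**Bias of one coached-versus-control contrast** if missing values are treated as missing at random (MAR): (rate in coached − rate in control) × d.
- T2: 0.03 × 0.5 = 0.015 SD, up to 0.07 × 1.0 = 0.07 SD.
- T1: those values × 10/36 = 0.004 and 0.019 SD.
- Standard error at 29 per arm, adjusted for baseline with r = 0.5: √(2/29 × (1 − 0.25)) = 0.227 SD.
- Bias as a share of that error: 7% to 31% at T2, 2% to 9% at T1.
- If half the deficits have resolved by the time of recording, these figures halve.
- If rates and deficits are equal across arms, the difference is zero.

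A simulation (6,000 runs per setting, 38 per arm, likelihood analysis under MAR against full follow-up) gave 0.014 to 0.07 SD at T2 and 0.004 to 0.02 SD at T1. With equal rates of 5% or 10%, the result was within about 0.001 of zero. This confirms the formula; it says nothing about whether the assumed rates are right.

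**Precision from keeping these people**, by count alone.

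| Attendance at T2 | Recovered | Evaluable | Fall in SE |
|---|---|---|---|
| all | 4.6 to 8.7 | 91.6 to 95.7 | 2.5% to 4.7% |
| 70% (assumed) | 3.2 to 6.1 | 90.2 to 93.1 | 1.8% to 3.3% |

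At 70% attendance the removable T2 bias is about 0.01 to 0.05 SD. The recovered values would be more variable, which offsets some or all of the precision gain.

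**The case against.** **The wording may be loose.** In a condensed article, leaving the study may stand for stopping the intervention, with {18b} meant to apply, and being asked to leave is softer than being removed. This is possible for complications. It is harder to maintain for pregnancy, where the text says excluded and gives a reason. If {18b} was meant to apply, {11b} should say so.

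**Pregnancy is already a baseline exclusion.** So it is in {10}, together with a screen for medical contraindications. The screen should lower the rate of later complications, so the assumed rates may be too high. But a restriction at entry does not justify removing someone after randomisation. True pregnancy rates should not differ by arm, so that part of the rule costs data and real-world scope rather than biasing the contrast.

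**The analysis plan already deals with it.** Those removed stay in the ITT set through imputation, a missing-not-at-random (MNAR) mechanism is considered, and sensitivity analyses are promised. All this stands and softens the point. It cannot recover values that the trial could have observed.

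**Some could not be measured anyway.** Assessments are on site and the sensor is returned to the day clinic, so a person with a serious complication may be unable to attend. That is right, and it limits what rewording can recover.

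**A reader might infer that the rule biases the trial in favour of coaching.** The documents do not support that. They give no event rate, arm difference or PA deficit. Coaches also watch for and report adverse events ({22}), so exits could be noticed sooner in the coached arms, but that is an inference and not a stated fact.

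**Conclusion.** The point holds as a design weakness in the stated rule. Followed as written, {11b} drops randomised participants for reasons tied to the primary outcome, and {18b} does not bring them back. This conflicts with the real-world purpose given for the ITT analysis.

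The size is probably small. The 5 to 9 exits and the 0.015 to 0.07 SD at T2 rest wholly on assumed rates and deficits. Between-arm bias arises only if exit rates or deficits differ by arm. No sample size, power or alpha statement is shown to be wrong by this point. The case for acting is that part of the loss is avoidable at low cost, so the change should be made but is not critical.

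**What to change.** Reword {11b} so that its consequence falls on the intervention:

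- For the listed complications and for pregnancy, coaching and the ergometer test are stopped, paused or adapted on a physician's advice. The dose rationale already allows coaching to go down to light-intensity movement.
- Accelerometer, interview and questionnaire assessments at T1 and T2 continue as in {18b}, where the participant is able and consents.
- These events are used only to define exclusion from the per-protocol set. Inclusion in the ITT set is already planned and needs no change.

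The cost is a short amendment with ethics approval ({25}), with no new visits or staff. One field for the reason and date of stopping coaching may be needed if existing records do not hold them. Whether the consent form must change cannot be seen from the article. The downsides are slightly more outcome variability, a possibly slightly smaller estimated effect, and missing ergometer values for these people. Recruitment began in June 2025 and only events after approval are covered, so the benefit is a few participants at most and shrinks with delay.
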